## Abstract

**Background:**

There is a pressing need for scalable healthcare solutions and a shift in the rehabilitation paradigm from hospitals to homes to tackle the increase in stroke incidence while reducing the practical and economic burden for patients, hospitals, and society. Digital health technologies can contribute to addressing this challenge; however, little is known about their effectiveness in at-home settings. In response, we have designed the RGS@home study to investigate the effectiveness, acceptance, and cost of a deep tech solution called the Rehabilitation Gaming System (RGS). RGS is a cloud-based system for delivering AI-enhanced rehabilitation using virtual reality, motion capture, and wearables that can be used in the hospital and at home. The core principles of the brain theory-based RGS intervention are to deliver rehabilitation exercises in the form of embodied, goal-oriented, and task-specific action.

**Methods:**

The RGS@home study is a randomized longitudinal clinical trial designed to assess whether the combination of the RGS intervention with standard care is superior to standard care alone for the functional recovery of stroke patients at the hospital and at home. The study is conducted in collaboration with hospitals in Spain, Sweden, and France and includes inpatients and outpatients at subacute and chronic stages post-stroke. The intervention duration is 3 months with assessment at baseline and after 3, 6, and 12 months. The impact of RGS is evaluated in terms of quality of life measurements, usability, and acceptance using standardized clinical scales, together with health economic analysis. So far, one-third of the patients expected to participate in the study have been recruited (*N* = 90, mean age 60, days after stroke ≥ 30 days). The trial will end in July 2023.

**Discussion:**

We predict an improvement in the patients’ recovery, high acceptance, and reduced costs due to a soft landing from the clinic to home rehabilitation. In addition, the data provided will allow us to assess whether the prescription of therapy at home can counteract deterioration and improve quality of life while also identifying new standards for online and remote assessment, diagnostics, and intervention across European hospitals.

**Trial registration:**

ClinicalTrials.gov NCT04620707. Registered on November 3, 2020

## Background

Stroke is the second leading cause of death worldwide and the primary contributor to the burden of neurological disease [1, 2]. According to the World Stroke Organization [3], there are over 13.5 million stroke cases every year, of which roughly 40% require rehabilitation, and the total world population of chronic stroke survivors is estimated at 80 million. These growth trends constitute a true crisis for healthcare systems which calls for new solutions to reduce costs, increase sustainability, and obtain better patient outcomes [4]. In addition, the COVID-19 crisis has caused a tremendous strain on stroke care and denied stroke patients necessary rehabilitation [5]. This demonstrates how health crises can deeply disrupt healthcare and the need to create more resilient systems. Digital health services have the potential to directly contribute to answering these challenges. Yet, this does require their alignment with the patient journey and its varying requirements in the clinic and at-home phases of rehabilitation, including the formulation, validation, and adoption of remote interventions and digital health strategies. Telerehabilitation has emerged as a promising solution for stroke rehabilitation, and several studies have shown promising results but also fundamental methodological limitations [6]. Most of these studies are underpowered, do not test or monitor patients at the clinic as inpatients and in their homes, or have follow-up measurements beyond the intervention period. In addition, most studies usually do not evaluate the cost-effectiveness of the intervention [7]. The RGS@home trial aims to address these shortcomings, focusing on the patients’ improvement of independence and quality of life by reducing the limitations of activities of daily living (ADL).

We have designed and implemented the validation of an e-health rehabilitation intervention for stroke patients and assessed its clinical impact, usability, and acceptance aligned with the patients’ journey to recovery. The technology included in this study capitalizes on RGS (Fig. 1), a cloud-based platform ​for delivering AI-enhanced rehabilitation protocols using virtual reality (VR), motion capture, wearables, and mobile apps that can be used in the hospital and at home. The core principles of the brain theory-based RGS intervention are to construct rehabilitation exercises in the form of embodied goal-oriented and task-specific actions [8]. The RGS platform uses AI techniques to individualize the exercises, VR for their delivery, and cloud and edge computing for data processing and storage. Thus far, interventions using RGS have been shown to be effective in enhancing functional recovery in acute, subacute, and chronic stroke patients [9] in several domains, i.e., motor [10–12], cognitive [13], language, and affect [14]. In addition, chronic stroke patients that trained with RGS improved their performance of ADL compared to a control group, and these changes correlated with cortical reorganization [15, 16].

**Fig. 1 Fig1:**
[figure not shown]
The Rehabilitation Gaming System (RGS) and its use during the patient’s journey to recovery. [Left] RGS consists of a touch screen computer, a motion capture system (Microsoft Kinect) to track the patient’s upper body movements while performing exercises in VR-based scenarios, a Leap Motion camera to track the movement of the hands, and the smartwatch RGSwear (either Fossil, TicWatch Pro, or Apple iWatch, which may be paired or not with a smartphone) to track the movement of the paretic arm. [Right] The RGSwear reminds the patient to perform circular movements every other day and displays the progress of the paretic arm

### Study rationale and hypotheses

This study proposes that deterioration after stroke (poor quality of life and function) can be counteracted by enabling the patients to continue their rehabilitation regime at home and monitoring their activities to stay engaged and train daily. We assess the RGS solution’s effectiveness, acceptance, and cost-effectiveness along with post-stroke monitoring and care continuum (Fig. 2). To achieve this goal, we use the RGS platform at the hospital, during the inpatient phase, and at the patients’ homes during the outpatient phase. The RGS platform includes a wearable device, the RGSwear, to track and promote the use of the paretic limb (Figs. 1 and 2).

**Fig. 2 Fig2:**
[figure not shown]
The RGS platform and its use during the patient’s journey to recovery. The RGS grants a continuum of care and rehabilitation, monitoring, and analytics that supports clinicians in their decision-making (Medical Information Management System (MIMS)) and stroke patients (inpatients and outpatients) and with a “soft-landing” from the hospital to home

RGS@home is a multicentric study, and the trial is conducted in three different hospitals across Europe, namely, Spain, Sweden, and France. Thus, this study will also provide insights into whether the proposed system can be used independently of country-specific practice, standards of stroke care, and reimbursement systems. We hypothesize that the RGS setup combined with conventional therapy will be a more effective rehabilitation program than conventional therapy alone. More specifically, we expect the combined approach to show high adherence to treatment and higher effects on function and well-being, while costs will be reduced. A specific effect we seek to reveal is the positive feedback between rehabilitation, ADLs, and recovery, which we see as a process that can overcome deterioration which can be achieved with e-health solutions. We hypothesize that spontaneous use of the paretic limb, as measured with the RGSwear wearable, is predictive of recovery.

## Trial status

The RGS@home protocol was approved by the local Ethical Committee of the three participating hospitals, in Spain, Sweden, and France. Recruitment began in November 2020 and is to be completed in July 2022. The study will end in July 2023. The study was registered on November 3, 2020, at ClinicalTrials.gov (NCT04620707).

## Method

### Study design

The RGS@home study is a randomized controlled trial (RCT) with stroke patients recruited from three hospitals in Spain, Sweden, and France. This RCT compares the impact of the intervention with the RGS platform plus standard care versus standard care alone. The standard care was provided to the patient as recommended in each hospital, on primary and secondary outcomes (see the “Outcome measures” section).

### Participants and recruitment

This RCT includes stroke patients (age 20–85 years old) at the subacute and chronic stages of the disease that are recruited voluntarily among patients admitted to the stroke rehabilitation units of Parc Sanitari Sant Joan de Déu (PSSJD, Barcelona, Spain), Uppsala University Hospital (UUH, Uppsala, Sweden), and the Centre Hospitalier Universitaire de Limoges (LIM, Limoges, France). The study experienced delays in the recruitment process due to the situation enforced in the hospitals by the COVID-19 health crisis.

The RGS@home trial protocol adheres to the international guidelines (Declaration of Helsinki, Edinburgh, 2000; Council of Europe Convention for the Protection of Human Rights and Dignity of Human Being concerning the Application of Biology and Medicine, Oviedo, 1997; Universal Declaration on Bioethics and Human Rights adopted by UNESCO’s General Conference on 19 October 2005).

### Inclusion criteria

Clinicians in each country perform a pre-selection to identify potential patients for the study. Those patients giving consent and signing the informed consent form are screened for inclusion according to the inclusion and exclusion criteria defined in Table 1.

**Table 1 Tab1:** Inclusion and exclusion criteria

**Inclusion criteria**	
Patients presenting a first-ever ischemic or intracerebral hemorrhagic stroke	
A CT scan and/or MRI to exclude other pathologies	
Lesion localization by clinical symptoms/signs	
Moderate to mild proximal upper limb motor impairment (MRC ≥ 2) and/or moderate to severe non-fluent aphasia (Barcelona test or equivalent)	
Age 20–85 years old	
Able to sit on a chair or a wheelchair interacting with RGS during a full session and be capable and willing to participate in RGS therapy	
**Exclusion criteria**	
Presence of a condition or abnormality that, in the opinion of the investigator, would compromise the safety of the patient or the quality of the data	
Severe cognitive capabilities preventing the execution of the experiment (MoCA < 19), but the final decision is under the clinician’s criterion	
Arteriovenous malformation or lesions not related to a stroke	
Severe associated impairment such as proximal but not distal spasticity, communication disabilities (sensory, Wernicke aphasia, or apraxia), major pain or other neuromuscular impairments, or orthopedic devices that would interfere with the correct execution of the experiment (Modified Ashworth Scale < 3)	
Unable to use RGS independently according to the clinician’s observations and lacking support from a caregiver to use RGS	
Refusal to sign the informed consent form	
Pre-stroke history of upper limb motor disability	

### Allocation and blinding

After being assessed for eligibility, patients are randomly allocated to either the intervention or control group (allocation ratio 2:1). The larger sample size in the experimental group allows more variables to be tested and gives more power to detect relevant effects in the experimental intervention. Randomization is realized via an adaptive stratified sampling (i.e., minimization) through the computerized encrypted cloud-based database (electronic case report form (eCRF)), which takes into account three conditions to balance the two groups: (1) time since stroke (≥ 30 days), (2) age (≥ 20 years old), and (3) severity (≥ 2 MRC). The allocation is concealed while patients and clinicians (except those involved in the baseline assessment) are not blind to the group allocation. A sham group was excluded from the design because an earlier study has shown a superior rehabilitation effect of training with RGS over sham computer game training using the Wii gaming console [10]. Since this is a first-of-a-kind study evaluating the outcomes (see Tables 2 and 3.) of an AI platform for rehabilitation, the sample size has been determined by feasibility (3 years) and estimated by considering the monthly number of eligible inpatients and outpatients of the participating hospitals. We plan to include a total of 90 patients via the clinical partners in the consortium. Each hospital will be recruiting 30 patients, 20 in the intervention group and 10 in the control group.

**Table 2 Tab2:** Study procedure and assessment

Study procedure	Screening and baseline assessment		Control group, standard care	Intervention group, 0–3 months daily sessions of 24 min or more	Post-treatment assessment		
	Inpatients	Outpatients			3 months	6 months	12 months
Informed consent	x	x					
Medical history	Patients’ demographics MRI/CT scan when available						
Assessment: domains and scales							
Disability and impairment	Barthel Index (BI)				x	x	x
	Stroke Impact Scale (SIS)				x		x
	Fugl-Meyer Assessment of the upper limb (UE-FM)				x	x	x
	Chedoke Arm and Hand Activity Inventory (CAHAI)				x		x
	Hamilton Depression Rating Scale (HDRS)				x		x
	Visual analog score (VAS) for pain				x		x^a^
	Modified Ashworth Scale (AS) for spasticity				x^a^		x
	Fatigue Severity Scale (FSS)				x		x
	Grip force^a^				x^a^		x^a^
	Kinematics from the motion capture camera of the RGS@home system				x	x	x
	RGSwear data (paretic arm)				Continuous		
	Incidents related to use				x		x
	Number and reason of dropouts				x		x
	Acceptability and usability Questionnaire for patients and physicians.				x	x	x
Quality of life	Stroke Specific Quality of Life scale (SSSQOL)				x		x
	Number of falls				x	x	x
	Short-Form-36 (SF-36)				x	x	x

^a^Included in the eCRF but not in the trial registry

**Table 3 Tab3:** Additional variables collected via eCRF

Assessment		3 months	6 months	12 months
Readmission	Number of outpatients that return to the hospital after discharge	x	x	x
	Reason for readmission	x	x	x
	Days of hospitalization due to readmission	x	x	x
	Costs of readmission	x	x	x
	Presence of CVA risk markers such as waist to hip ratio, smoking cessation, blood pressure, hypertension, and blood markers	x	x	x
Cost of treatment	Total cost of therapy	x		x
	Hours of therapy	x		x
	Total cost of traveling from home to hospital	x		x
	Hours of traveling from home to hospital	x		x
	Number of days of inpatient hospitalization	x		x
Quality of life	Return to work	x	x	x
	Number of formal caregiver hours per week	x	x	x
Acceptability	Number of hours of system use at home	x		x
	Number of hours technical/visits to patients’ home	x	x	x
	Number of equipment replacements	x		x
	Incidents related to use	x		x

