**Fig. 3 Fig3:**
[figure not shown]
Clinical trial timeline. Participants are recruited as inpatients shortly after a stroke or as outpatients after hospital discharge. After a pre-selection, participants receive baseline evaluations and are randomly assigned to the intervention group or control group. The inpatients start using the RGS desktop setup during their stay at the hospital, while the outpatients use RGS directly in their homes. All participants in the intervention group are provided with a wearable device (RGSwear) for continuous monitoring. The control group receives rehabilitation as usual according to the standard care of the countries included in the study. According to the outcome measures assessments, all participants are evaluated again at 3, 6, and 12 months after baseline evaluation (see Tables 2 and 3)

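### The printed minimisation bounds for age and severity coincide with entry limits, so age is not balanced and severity hardly; hospital is not a listed factor although 20:10 per hospital is planned

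*Protocol article*

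**What the plan says.** The Allocation and blinding section describes 2:1 allocation by minimisation through the eCRF and gives the factors on which the groups are to be balanced as "1) time since stroke (≥ 30 days), (2) age (≥ 20 years old), and (3) severity (≥ 2 MRC". One bound is printed per factor, and no other factor is named.

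Other parts of the protocol article bear on this:

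- **Table 1, age:** "Age 20–85 years old".
- **Table 1, severity:** "Moderate to mild proximal upper limb motor impairment (MRC ≥ 2) and/or moderate to severe non-fluent aphasia (Barcelona test or equivalent".
- **Time since stroke:** Table 1 sets no minimum. The abstract's Methods paragraph has, in a parenthesis about the patients, "days after stroke ≥ 30 days". The Fig. 3 legend says "Participants are recruited as inpatients shortly after a stroke or as outpatients after hospital discharge".
- **Split by hospital:** "Each hospital will be recruiting 30 patients, 20 in the intervention group and 10 in the control group", for 90 patients in total.
- **Standard care:** the Intervention and control groups section says that it differs between countries and with the patient's condition.
- **Analysis:** the Statistical method section compares change in the Barthel Index between groups. It names covariates only for readmission.

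**The concern.** Minimisation acts on a factor only if patients can differ in its level. A bound that every eligible patient satisfies gives a factor with one level, and that factor has no influence on who goes where. If the algorithm is coded as printed, the article claims balance on age and severity that it does not deliver, or barely delivers.

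Hospital matters for a different reason. The control treatment is local standard care, so site is plausibly prognostic, and a fixed split per site is planned. Nothing in the printed rule produces that split.

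With only 30 controls, chance differences in age, severity or site can be large enough to cloud the reading of the Barthel result.

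**Working it through.** **1. The plan's own total.** 3 hospitals × (20 + 10) = 90, and 60:30 = 2:1. This reproduces. The sample size rests on feasibility, so there is no power calculation to check.

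**2. Does each printed bound split the eligible patients?**

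| Factor | Printed bound | Entry rule | Can it separate patients? |
|---|---|---|---|
| Age | ≥ 20 years | 20–85 years (Table 1) | No, 100% satisfy it |
| Severity | MRC ≥ 2 | MRC ≥ 2 and/or non-fluent aphasia (Table 1) | Only aphasia-only entrants below MRC 2; share not given |
| Time since stroke | ≥ 30 days | None in Table 1 | No, if the abstract's 30 days is an entry limit; possibly yes, if inpatients enter earlier, as Fig. 3 suggests |
| Hospital | Not listed | – | Not used, as printed |

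**3. Chance balance of a factor that is not controlled, arms 60:30.**

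- SE of a standardised baseline difference = √(1/60 + 1/30) = 0.224 SD.
- P(difference beyond ±0.3 SD) = P(|Z| > 0.3/0.2236) = P(|Z| > 1.34) = 0.18.
- At least one of two independent factors (age, severity): 1 − (1 − 0.18)² = 0.33.
- For a 50/50 binary characteristic, the SD of the arm difference is 0.5 × 0.2236 = 11.2 percentage points. The mean absolute difference is 0.798 × 11.2 = 8.9 points, and the 95th percentile is 1.96 × 11.2 = 21.9 points.

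**4. Split by hospital, total fixed at 60:30, 30 patients per hospital, hospital ignored.** The number of controls at one hospital is hypergeometric.

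- P(exactly 10 controls at one hospital) = C(30,10) × C(60,20) / C(90,30) = 0.187.
- P(exactly 10 at all three) = C(30,10)³ / C(90,30) = 0.040.
- SD = √(30 × 1/3 × 2/3 × 60/89) = 2.12. The 95% range is 6–14 controls, that is, 16–24 in the RGS arm.

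**5. Simulation (4,000 trials of 90, biased-coin minimisation at 2:1).** These assumptions are not in the article: 30 patients per site in random order; assignment to RGS with probability 0.9, 2/3 or 0.2 according to the imbalance; age and severity split 50/50; 30% of patients on one side of the time cut.

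| Factors that split the sample | Mean absolute arm difference (percentage points) | All sites 20:10 | Some site off by ≥ 3 |
|---|---|---|---|
| None | Age 9.1, severity 8.8, time 8.1 | 3% | 47% |
| Time only | Age 9.0, severity 9.0, time 2.2 | 3% | 47% |
| All three | About 2.2 each | 2% | 46% |
| All three plus hospital | About 2.6 each | 25% | 2.5% |

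The 95th percentile is 20–22 points for an uncontrolled factor, about 5–6 for a controlled one without hospital and about 7 with hospital added. In the first row the RGS total still has an SD of only 0.4 patients, so the overall ratio is held even when no factor splits the sample.

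**The case against.** The strongest reply is that the brackets may show each variable's eligible range and not the coded levels. The working levels could sit in the eCRF specification or the full protocol, and the algorithm could run separately in each hospital, which would keep each site close to 20:10. This is possible, and the article does not exclude it. But the article does not say so either. It presents these bounds as the conditions used for balancing. A rule printed in a form that cannot do its stated job is more than a detail left to another document.

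Three further replies stand in whole or in part.

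- **Time since stroke.** A reader might infer that all three factors sit at entry thresholds and that the algorithm balances nothing. The documents do not support this. The 30-day bound is absent from Table 1, the Fig. 3 legend points towards earlier recruitment of inpatients, and the overall 2:1 ratio is controlled in any case. A three-factor figure, 1 − (1 − 0.18)³ = 45%, would need time since stroke to be inert as well.
- **Severity.** The aphasia route allows MRC below 2. Its share is not given, so it cannot be called negligible.
- **Consequences.** Chance imbalance under concealed random allocation costs precision and makes the result harder to interpret; it does not bias the comparison. Using change in Barthel takes partial account of baseline Barthel. Covariate adjustment may be set out in an analysis plan that is not shown.

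Inpatient or outpatient status as a further factor, or a particular age cut, is a matter of preference. Hospital is different, because the article itself commits to a split by hospital.

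**Conclusion.** The point holds in limited form. Followed as printed, minimisation cannot balance age and can act on severity only through aphasia-only entrants. For motor-route patients both are left at chance balance: SE 0.224 SD, each off by more than 0.3 SD in 18% of trials, and at least one of the two in about 33%, treating them as independent.

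Time since stroke is unresolved. The abstract, Table 1, the Allocation and blinding section and the Fig. 3 legend have to be reconciled before anyone can say whether it works as a factor.

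The 20:10 split does not follow from the stated rule. It has probability about 19% at one hospital and about 4% at all three, assuming 60:30 overall, 30 patients per site and no per-hospital run.

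A reader might also infer that the allocation is biased or the test invalid. Nothing in the article supports that.

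**What to change.** - For further patients, use levels of age, severity and time since stroke that each divide the eligible population, and state them. Code patients already enrolled at the same levels, so that the running totals include them.
- Reconcile the 30-day bound across the abstract, Table 1, the Allocation and blinding section and the Fig. 3 legend.
- Add hospital as a minimisation factor or a stratum.
- Adjust the Barthel comparison for age, severity, time since stroke and hospital in all patients. This also covers those already allocated, and helps however much recruitment remains.
- If the eCRF already uses such levels, or runs separately in each hospital, correct the text to say so; the allocation itself then needs no change on that point.

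The cost is a small eCRF change or a text correction, one amendment line, and slightly looser balance per factor once hospital is added (about 2.6 against 2.2 percentage points in the simulation). The variables are already recorded at baseline or screening.

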### Timeline patients’ assessment

The RGS@home RCT is a longitudinal study that recruits and assesses stroke patients at different time points after stroke (Fig. 3). All patients are evaluated on primary and secondary outcome measurements by trained clinicians (different from those that performed the baseline assessment) at the respective hospital.

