#### Primary outcome measures

One main outcome measure is calculated as a compound score summarizing the main outcome of each of the 5 domains: (1) disability and impairment (Barthel Index for independence in activities of daily living), (2) readmission (number of patients who return to the hospital (inpatient) after being discharged to at-home status), (3) cost of treatment (total cost of the therapy), (4) quality of life (the Stroke Specific Quality of Life Scale), and (5) acceptability (amount of use at home).

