## Data collection and management

The clinical outcome measurements and the patients’ data are collected by each participating hospital by blinded clinicians and logged in the eCRF. Data obtained through the interaction with the RGS ecosystem is automatically logged in the MIMS. The data in the eCRF is securely stored and anonymized (patients are assigned an ID), and monitoring is organized by each clinical partner independently, adhering to local standards and procedures. To ensure all data is logged correctly and no duplicates exist, the RGS@home eCRF process automatically checks to ensure that the logged scores of the clinical scales and tests are valid. Two workshops have been organized with the study coordinators to understand how the assessments are performed and the data collected.

The data obtained from the interaction with the RGS ecosystem (kinematic data, prescriptions, protocol events, and use) is automatically stored in the MIMS, a secured cloud-based database that the participating hospitals can access via a web browser with a username and password. Within the MIMS, and separately from the eCRF, the participating hospitals can create profiles (anonymized) for each patient, determine and manage the prescriptions of exercises, and track the patient’s progress through dashboards, graphics, and analytic reports. The sponsor can remotely access the password-protected data in the MIMS to analyze the interaction with the RGS system.

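### The protocol contradicts itself on whether the clinicians who score the 3-, 6- and 12-month outcomes are blind to allocation

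*Protocol article*

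**What the plan says.** Three sections of the protocol article describe who is blind and who scores outcomes.

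- **Allocation and blinding:** "patients and clinicians (except those involved in the baseline assessment) are not blind to the group allocation". The only blinded people named are the clinicians who do the baseline assessment. The same section explains why there is no sham group.
- **Timeline patients' assessment:** all patients are "evaluated on primary and secondary outcome measurements by trained clinicians (different from those that performed the baseline assessment) at the respective hospital".
- **Data collection and management:** the clinical outcome measurements "are collected by each participating hospital by blinded clinicians and logged in the eCRF".

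The legend of Fig. 3 gives the sequence. First, "participants receive baseline evaluations and are randomly assigned to the intervention group or control group"; later, "all participants are evaluated again at 3, 6, and 12 months after baseline evaluation". Primary outcome measures puts the "Barthel Index for independence in activities of daily living" into the compound main outcome. Statistical method also gives the Barthel Index its own between-group comparison.

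**The concern.** In an open-label trial, blinding matters for an assessor at the visits after allocation. The section devoted to blinding grants it only to the baseline assessors, and another section says that different people score the outcomes. A site that followed those two sections to the letter would have unblinded raters at every follow-up visit, while a reader of the data section would believe the opposite.

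What is at stake is detection bias on scales that need a clinician's judgement. By Table 2, the Barthel Index and UE-FM are scored at 3, 6 and 12 months, and the CAHAI, HDRS and Modified Ashworth Scale at 3 and 12 months. The arm would not be hard to learn. Intervention patients keep the RGSwear for up to a year after recruitment, hospital clinicians prescribe and follow RGS training in the MIMS, and the eCRF that holds the outcomes also runs the randomization and holds fields on home use of the system. If ratings were shifted by knowledge of the arm, the analysis could not separate that shift from a treatment effect.

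**Working it through.** **Consistency check**

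1. Blinded clinicians are the baseline assessors and nobody else (Allocation and blinding).
2. Outcome assessors are not the baseline assessors (Timeline patients' assessment). That sentence does not name the visits. They follow from its contrast with baseline and from the 3-, 6- and 12-month schedule in the Fig. 3 legend.
3. From 1 and 2, the 3-, 6- and 12-month assessors are not blind.
4. Clinical outcomes are collected by blinded clinicians (Data collection and management). This contradicts step 3.
5. Step 4 cannot be rescued by reading it as baseline only, because Outcome measures says the outcomes are collected at four time points. No other section reconciles the statements.
6. The Fig. 3 legend lists baseline evaluation before random assignment. At that point there is no allocation to know, so the masking described in step 1 protects no follow-up rating.

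**Illustration of size**

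The article gives no Barthel SD, no expected rating shift and no power calculation (the sample size rests on feasibility), so there is no figure of the plan to reproduce. Inputs:

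- Group sizes of 60 and 30: from the article, three hospitals with 20 intervention and 10 control patients each. All are taken as analysed.
- SD of 20 Barthel points: assumption.
- Rating shift of 2, 3 or 5 points between arms with no true effect: assumption.
- Two-sided test at 5%, critical value 1.96: assumption.

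Standard error in SD units: √(1/60 + 1/30) = √0.05 = 0.2236.

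Expected z: (shift / 20) / 0.2236.

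Rejection probability: Φ(−1.96 + z) + Φ(−1.96 − z).

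| Shift (points) | Shift in SD | z | False-positive rate |
|---|---|---|---|
| 0 | 0 | 0 | 5.0% |
| 2 | 0.10 | 0.447 | 7.3% |
| 3 | 0.15 | 0.671 | 10.3% |
| 5 | 0.25 | 1.118 | 20.1% |

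Only the ratio of shift to SD enters. A larger SD lowers these rates and a smaller SD raises them.

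**The case against.** The strongest reply is that the data section is the one that directly describes who collects the outcomes, and it says they are blinded. The exception in the blinding section may simply be misworded: masking only the people who assess before randomization makes little sense, and follow-up assessors may have been meant. Using different people at follow-up also fits an attempt at independent assessment. This stands. A reader might infer from the first two sections that outcomes are in fact scored unblinded, but the article does not support that as a statement of practice. It supports only that the sections conflict.

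A second reply concerns the size. The main outcome is a compound over five domains. Readmission, therapy cost and logged home use do not depend on a rater in the same way, and the self-reported quality-of-life scale is open to bias from unblinded patients whatever the assessor knows. Disability outcomes are to be analysed as normalized improvement, not raw points. This also stands: a reader might take the rates above as the error rate of the trial's primary analysis, and they are not. That the bias would favour the device is plausible, but the article does not establish it.

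A third reply is that the rule on different assessors is sound. It keeps raters from anchoring on their own baseline scores, and separate raters can be masked just as well. That is right, and the rule need not go.

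None of this removes the contradiction. Nor is it a detail that an article leaves to a fuller document: the article makes positive statements about masking, and they disagree.

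**Conclusion.** The article conflicts with itself on the masking of follow-up assessors. Its blinding section, as written, protects none of the ratings made after randomization. That needs correcting whichever practice is in use. If the sites do use masked raters, the wording is wrong. If they do not, the clinician-rated scales carry a risk of bias that analysis cannot remove.

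The contradiction rests on the text alone and needs no assumption. The size of any bias is unknown. The rise from 5% to about 7%, 10% or 20% is an illustration for a raw Barthel comparison under the assumed shifts and a single assumed SD.

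**What to change.** - In Allocation and blinding, state that the clinicians who score the 3-, 6- and 12-month outcomes are masked to allocation and are not involved in the patient's RGS treatment. Existing staff can fill this role.
- Leave the different-assessor rule in Timeline patients' assessment if the sites prefer it, and bring that section and Data collection and management into line with the corrected statement.
- Ask patients not to reveal their arm to the assessor.
- Establish what has been done so far. If any visits were scored unblinded, record this by visit and report a sensitivity analysis. If every visit so far was unblinded, excluding them would leave no follow-up ratings from that period, and the report should say so.

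The cost is a change of wording and, where current raters know the allocation, some reassignment across three hospitals while the trial runs. That would mix masked and unmasked ratings within the trial, which is one reason to record masking status by visit. The Discussion says about one-third of patients are included so far, and the trial runs to July 2023, so much of the follow-up could still be covered.
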